### Outcomes

Primary outcome and secondary outcomes are detailed in Table 3. The methods for assessing efficacy include:

**Table 3 Tab3:** Outcome measures

Primary outcome
Cumulative mortality to 28 days for the transfusion strategy comparison, and to 180 days for the nutritional support/antibiotic prophylaxis comparison
Secondary outcomes
Mortality: at 48 hours, 28 days, 90 days and 180 days (cumulative) where not the primary outcome
Morbidity: endpoints relating to the specific mechanisms of action of each intervention:
re-admission to hospital
haematological:
proportion achieving correction of anaemia (defined by the WHO as Hb > 9 g/dl) at 48 hours, 28 days, 90 days and 180 days
development of new profound anaemia (Hb < 4 g/dl) during acute admission or development of severe anaemia (Hb < 6 g/dl) post discharge
nutritional: changes in weight and mid-upper arm circumference (MUAC) at 90 days and 180 days
anti-infection: changes in inflammatory markers (C-reactive protein (CRP) , procalcitonin), incidence of bacterial infections and malaria at 28 days, 90 days and 180 days
solicited adverse events: suspected transfusion reactions: febrile reactions, TRALI (Transfusion Related Acute Lung Injury) (any grade); grade 3–4 toxicity of cotrimoxazole, MVMM or standard iron/folate
serious adverse events
costs and cost-effectiveness

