### Sample size calculation and statistical analysis

#### Sample size

The sample size calculation is based on the following assumptions:80 % power, 2-sided alpha = 0.013 to allow for 4 comparisons (see below)SA cases are 50 % complicated (< 4 g/dl or 4–6 g/dl with prostration/respiratory distress/known sickle cell disease/haemoglobinuria) and 50 % uncomplicated (4–6 g/dl without prostration, respiratory distress, known sickle cell disease or haemoglobinuria) [12] (and [name] personal communication)Mortality (cumulative) at 48 hours and 4 weeks is 11 % and 16 % respectively in complicated SA, and 4 % and 9 % in uncomplicated SAThe cumulative rate of re-admission, SA relapse and re-transfusion at 6 months is 12.5 % in both complicated and uncomplicated SA (in addition to mortality above)For the primary comparison of transfusion versus no transfusion in uncomplicated SA at 4 weeks, the minimum clinically relevant difference is a 50 % relative reduction (R1b): for the other primary comparison of transfusion volume (20 versus 30 ml/kg) at 4 weeks (R1a and 1b), the minimum clinically relevant difference is a 30 % relative reduction. The minimum clinically relevant difference is larger for the transfusion versus no transfusion question as provision of safe blood at all will require greater resources than provision of slightly larger versus slightly smaller blood volumes. As the same relative difference translates to a far larger absolute difference at higher event rates, for the primary comparison at 6 months (R2/3) the minimum clinically relevant difference is a 5 % absolute reduction (see below for control group event rates). Then:(R1b) comparison of transfusion versus no transfusion (50 % reduction from 9 % control mortality at 4 weeks) requires 1460 uncomplicated SA cases (1:1 allocation to 30/20 ml/kg:no transfusion, 730 in no transfusion group, 365 receiving 20 ml/kg and 365 receiving 30 ml/kg transfusions)(R1a and 1b) if the overall ratio of uncomplicated:complicated SAs is 1:1 (ie 50 % of each type), then within the subgroup randomised 1:1 to 30 versus 20 ml/kg, the ratio will be 1:2 because this comparison excludes the 50 % of uncomplicated SA randomised to no transfusion. Overall mortality at 4 weeks in this group will, therefore, be 13.67 % (0.33 × 9 % + 0.67 × 16 %). The comparison of 30 versus 20 ml/kg (30 % reduction, to 9.57 %) requires 2798 SAs, 1399 per group (split 466 uncomplicated, 933 complicated)Therefore, comparing required sample sizes for R1a and R1b, to address both parts of the transfusion question (R1) we need slightly more uncomplicated SA children per group from (R1a and 1b – *n* = 466) than (R1b – *n* = 365), and therefore the total sample size is 3730 cases (933 × 2 = 1866 complicated, 466 × 4 = 1864 uncomplicated)(R2/3) the comparison of multi-vitamins versus SOC (1:1) and cotrimoxazole prophylaxis versus SOC (1:1) requires 3162 SA cases, assuming 50 % are complicated and 50 % uncomplicated, to detect a 5 % absolute reduction from average control mortality of 25 % (0.5 × 21.5 % + 0.5 × 28.5 % at 4 weeks).

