
Thus, a sample size of 3730 SA cases would allow the multiple comparisons above to be made. Assuming a 6 % loss to follow-up by 6 months increases this to 3954 SA cases. As the effect sizes are reasonably large on the relative scale (> 30 % reduction), inflation factors which adjust for the factorial design are close to 1. However, assumptions are more sensitive to the relative contribution of uncomplicated:complicated SA. Capping the uncomplicated SA strata at 2000 cases (ie recruiting at least 1950 complicated SA) retains at least 80 % power to detect the differences above independently of variations in the contributing proportions of complicated SA.

Randomising uncomplicated SA (R1b) 1:1:2 between 30 ml/kg:20 ml/kg:no transfusion provides greater power for the comparison of no transfusion (SOC) versus transfusion in this group because the final randomisation ratio for transfusion:no transfusion is 1:1. In contrast, a 1:1:1 randomisation in this strata would produce a 2:1 transfusion:no transfusion ratio which has lower power.

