Secondary outcome measures will be analysed using time-to-event methods or normal linear regression for continuous variables. The frequency of hospital re-admissions and adverse events will be tabulated by body systems and by randomised groups, and the number of events experienced by each participant will be compared across randomised groups using Fisher’s exact test.

For the within-trial cost-effectiveness analysis, the differential cost of the treatment interventions will be related to their differential outcomes in terms of the primary outcome. The relative cost-effectiveness of the alternative forms of management will then be assessed using standard decision rules and a full stochastic analysis will be undertaken. A cost-utility analysis will also be conducted using a standard approach. The within-trial analysis will be augmented by extrapolation beyond the trial follow-up using decision-analytic modelling. The aim of this analysis will be to predict the implications of any difference in clinical endpoints in the trial for subsequent quality-adjusted survival duration and long-term resource costs. This will inform the question of whether any differences in drug costs between the treatment groups are offset by reduction in other treatment costs or health improvements in the long term.

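### Fisher's exact test on the number of re-admissions and adverse events per child ignores the order of the counts and time at risk, so this supplementary comparison loses power and gives no rate ratio

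*Protocol article*

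**What the plan says.** The Statistical analysis section of the protocol article sets two rules for non-primary outcomes. The general one is: "Secondary outcome measures will be analysed using time-to-event methods or normal linear regression for continuous variables". The next sentence covers re-admissions and adverse events. They are to be tabulated by body system and arm, and "the number of events experienced by each participant will be compared across randomised groups using Fisher’s exact test". That sentence names no effect measure, no allowance for length of follow-up and no stratification.

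Table 3 lists "re-admission to hospital" as a morbidity outcome, and lists solicited and serious adverse events as secondary outcomes. The primary time-to-event analysis is stratified by centre and baseline severity. It compares transfusion with no transfusion in uncomplicated children only (R1b), and 20 with 30 ml/kg across both strata.

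The Sample size section assumes cumulative mortality of 11 % at 48 hours and 16 % at 4 weeks in complicated anaemia, and 4 % and 9 % in uncomplicated anaemia. It assumes a 12.5 % six-month rate of re-admission, relapse and re-transfusion combined, the same in both strata.

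**The concern.** The number of events per child is an ordered count collected over unequal time. Fisher's test on a count-by-arm table asks only whether the two distributions differ in any way. It spreads its power over all such differences instead of the one of interest, a higher or lower event rate. It returns a p-value without a rate ratio or interval.

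It also gives a child who dies on day 1 the same weight as a child followed for 180 days. If a treatment saves lives, its arm accrues more follow-up and hence more opportunity for later events, which an analysis of raw counts cannot separate from a higher event rate. What is at stake is how the re-admission and adverse-event counts are read. The method is stated in the article, so this is not a detail merely left to the analysis plan.

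**Working it through.** **1. The plan's own figures.** The article gives no power for the count comparison. Its sample sizes can be checked to confirm the design inputs. Per arm, n = [z(1−α/2)·√(2p̄(1−p̄)) + z(0.80)·√(p1(1−p1) + p2(1−p2))]² / (p1−p2)², with α = 0.013 two-sided, then the continuity correction n/4·[1 + √(1 + 4/(n·|p1−p2|))]².
- 9 % v 4.5 %: 730 per arm, total 1460 (stated: "50 % reduction from 9 % control mortality at 4 weeks) requires 1460 uncomplicated SA cases").
- 13.67 % v 9.57 %: 1399 per arm, total 2798 (stated: "30 % reduction, to 9.57 %) requires 2798 SAs, 1399 per group").
- 25 % v 20 %: 1581 per arm, total 3162 (stated: "cotrimoxazole prophylaxis versus SOC (1:1) requires 3162 SA cases").

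All three reproduce. 3730 × 1.06 = 3954, so R2 and R3 have 3954/2 = 1977 per arm.

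**2. Cost of ignoring order, in principle.** A 1-df test with 80 % power at α = 0.05 has noncentrality 7.85. If the same noncentrality is tested on more degrees of freedom, power is 70.9 % on 2 df, 64.5 % on 3 df and 59.5 % on 4 df.

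**3. Simulated power.** There were 600 trials per setting, 1977 per arm, half the children complicated, with 4-week deaths of 16 % and 9 % falling uniformly over days 0 to 28 of 180. Means, rate ratios (RR) and dispersion are assumptions. The first two rows give about 12 % to 13 % of control children an event, close to the 12.5 % composite used as a proxy for re-admission. The count-table test is the r × 2 extension of Fisher's test with a Monte Carlo p-value. The rate test uses log RR = log(Σy1/ΣT1) − log(Σy0/ΣT0), with robust variance Σ(y−λT)²/(Σy)² summed over arms. Power (%) at α = 0.05:

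| Counts | Fisher, all counts | Fisher, 0/1/2/3+ | Fisher, any v none | Wilcoxon | Rate model |
|---|---|---|---|---|---|
| Poisson, mean 0.155, RR 0.76 | 73 | 73 | 81 | 82 | 85 |
| Overdispersed, mean 0.17, RR 0.75 | 60 | 63 | 74 | 77 | 84 |
| Overdispersed, mean 0.5, RR 0.82 | 48 | 58 | 54 | 63 | 78 |
| Overdispersed, mean 1.0, RR 0.87 | 43 | 57 | 49 | 67 | 84 |

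- Re-admission-like rows, all counts v rate model: 85 − 73 = 12 and 84 − 60 = 24 points.
- The same rows, any v none: 85 − 81 = 4 and 84 − 74 = 10 points.
- Frequent events, all counts v rate model: 31 and 42 points from unrounded values (78.2 − 47.5 and 84.2 − 42.5).
- Against Wilcoxon, which adds only order: 9 to 25 points over the four rows.
- At α = 0.013, all counts v rate model: 15 to 39 points.

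Monte Carlo error is about 2 points.

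**4. Time at risk.** At a 1:1 mix, deaths by 48 hours average (11 + 4)/2 = 7.5 % and by 4 weeks (16 + 9)/2 = 12.5 %, so 60 % of the early deaths fall in the first two days. With deaths uniform over 28 days, a child who dies contributes on average 14/180 = 0.078 of full follow-up.
- Control arm: 1 − 0.125 × 0.922 = 0.885 of full follow-up.
- Arm with 30 % fewer deaths: 1 − 0.0875 × 0.922 = 0.919.
- Ratio: 0.919/0.885 = 1.04, so about 4 % more events are expected with no difference in rate.

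Simulated rejection at nominal 5 %, equal event rates and 30 % fewer deaths: for mean 0.17, about 6 % for Fisher's test and about 6 % for the rate model; for mean 1.0, 10 % to 15 % for Fisher's test depending on the table, against about 5 % for the rate model. These runs use the R2/R3 arm size, while a 30 % cut in 4-week deaths is the R1 volume target. Repeating the any-versus-none case for frequent events at 1399 per group, two thirds complicated, stays within 10 % to 15 %.

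**5. Strata.** Stratifying the rate model by severity changed power by at most 1 point when event rates were equal across strata, and added 3 points (77 % to 80 %) when they were set at 1.4 and 0.6 times the average.

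**The case against.** The strongest reply is that the sentence just before already covers the outcome. Secondary outcomes go to time-to-event methods, and re-admission is one of them, so first re-admission gets an analysis that censors follow-up and can give a hazard ratio. The Fisher comparison sits beside a tabulation by body system and is supplementary. This stands, and it limits the point to the count comparison. It does not make the named test suit counts.

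A second reply is that Fisher's test may be meant for any event versus none. The text says number of events, but if the other reading is intended the loss for re-admission falls to 4 to 10 points. A third is that the loss depends on distributions the article does not give, and that 12.5 % is a composite and not a re-admission rate. Both are fair, so the sizes are given as ranges.

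Some stronger readings are tempting but unsupported:
- **The test pools all three R1 groups and so mistakes severity for treatment.** The text says only that groups are compared. The primary R1 comparisons are defined so that transfusion versus none stays within uncomplicated children, and nothing says the count analysis departs from that. The article also assumes equal 12.5 % rates in both strata.
- **Omitting severity strata costs material power.** It costs 0 to 3 points, and none under the article's equal rates.
- **Better survival on R2 or R3 would hide most of a real benefit.** Those treatments start at discharge or day 5 and cannot change the early deaths that remove most follow-up. The time-at-risk problem belongs mainly to R1.
- **The arm with more deaths always shows fewer events.** The section on reducing bias counts deaths among serious adverse events, so a child who dies early is not a zero in those counts.

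**Conclusion.** The point holds for the supplementary comparison of re-admission and adverse-event counts. The stated test ignores order and time at risk and gives no effect size. The loss against a rate model is about 12 to 24 points of power for re-admission-like counts and 31 to 42 points for frequent events, or 4 to 10 points for re-admission if any versus none is meant. False rejection caused by unequal survival is negligible for rare events (about 6 %) and reaches 10 % to 15 % for frequent events when one arm has 30 % fewer deaths.

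These sizes rest on assumed means, dispersion and rate ratios. A reader might infer a fixed loss of about 20 points, or that these counts alone carry the safety conclusions. The article supports neither: it gives no count distribution, and it assigns secondary outcomes to time-to-event methods as well. The primary mortality analysis is unaffected.

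**What to change.** Compare per-child counts with a negative binomial model, or a recurrent-event model with robust variance. Use log time alive and followed as offset, adjust for centre and severity, and report rate ratios with intervals. State that the R1 contrasts are those of the primary analysis: transfusion versus none within R1b, and 20 versus 30 ml/kg across both strata. Keep Fisher's exact test for the proportion of children with at least one event where events are rare, and word it as a proportion.

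The cost is a change of wording and a little more programming. The drawback is reliance on a rate model.

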### Study design and population

TRACT is a multicentre randomised controlled trial of 3954 children aged 2 months to 12 years admitted to hospital with a Hb < 6 g/dl. Children will be enrolled over 2 years from 2 countries and followed for 6 months. The trial will simultaneously evaluate 3 ways to reduce short-term and longer-term mortality (primary endpoint) and morbidity following admission to hospital with SA in sub-Saharan Africa using a 3 x 2 x 2 factorial design. All randomisations will be open. Inclusion/exclusion criteria are detailed in Table 1.

**Table 1 Tab1:** Inclusion and exclusion criteria

Inclusion criteria	Exclusion criteria
Aged 2 months to 12 years	Malignancy or other terminal illness
Severe anaemia (Hb < 6 g/dl) on the day of admission to hospital	Acute trauma or burns as main reason for admission
Care-giver willing/able to provide consent	Surgery as main reason for admission
	Chronic renal or liver failure
	Signs of bi-ventricular heart failure
	Known congenital or valvular heart disease (non-surgically corrected)
	Children who are exclusively breast fed (thus unable to take nutritional support)

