#### Health economics

The trial will measure healthcare-related costs in trial participants, starting at randomisation and continuing for the duration of follow-up. Information on hospitalisations (number, reason, and duration of stay) and other healthcare resource utilisation (visits to healthcare centres, medications) will be collected by carer interview at the 28-day, 90-day and 180-day visits. The economic evaluation will be conducted from the health services perspective. Unit costs will be attached to resource use, using the best available estimates of long-run marginal opportunity cost, to obtain a cost per patient over the period of follow-up. Routinely available national unit costs will be used where possible with local estimations where necessary. There will also be a budget impact analyses of the consequences of adopting the interventions on the health sector budgets, in each of the countries of the trial.

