### Statistical analysis

The analyses will be described in detail in a full Statistical Analysis Plan. In brief, each intervention is hypothesised to be superior to SOC and, therefore, the proposed analysis is intention-to-treat, including all randomised patients. The primary analysis will compare: a) transfusion versus no transfusion (strata b only) and b) 20 ml/kg versus 30 ml/kg (strata a and b) in terms of the proportion of children with fatal outcome 28 days after randomisation. Primary outcome analysis will use time-to-event methods (Kaplan-Meier, log-rank test, proportional hazards models) to the timepoints specified for primary and secondary outcomes, stratified by centre and anaemia severity at baseline. Correction of anaemia will also be analysed using time-to-event methods.

Pre-specified subgroup analyses will include each of the other randomised allocations (ie exploration of interactions in the factorial design), together with the other randomisation stratification factor (centre) and the anaemia stratification factor (a versus b) for the transfusion randomisation. We will also investigate a priori whether there was any evidence for a different impact of the interventions according to the following categorical variables: previous receipt of a transfusion (ever or at another health centre in this illness); speed (rate) at which the transfusion is administered; fever; malaria; microbiological evidence of sepsis (blood culture or retrospective molecular diagnosis); HIV; known or previously undiagnosed sickle cell disease.

For the cotrimoxazole prophylaxis and MVMM supplementation randomisations the primary analysis will be intention-to-treat based on all randomised participants, as above. However, secondary analyses will be restricted to: (i) patients discharged alive, and (ii) patients discharged alive in whom these interventions were neither mandated nor contraindicated (ie excluding HIV-infected children and those with known GP6D deficiency from the cotrimoxazole randomisation, and excluding children admitted for severe acute malnutrition from the supplementation randomisation).

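### The within-trial cost-effectiveness analysis of the transfusion comparisons pairs costs to 180 days with deaths to 28 days

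*Protocol article*

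**What the plan says.** Three parts of the protocol article bear on this.

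- **Effect measure.** The Statistical analysis section states that, within the trial, "the differential cost of the treatment interventions will be related to their differential outcomes in terms of the primary outcome".
- **Period of that outcome.** Table 3, under Outcomes, defines it as "Cumulative mortality to 28 days for the transfusion strategy comparison, and to 180 days for the nutritional support/antibiotic prophylaxis comparison". The Statistical analysis section confirms the R1 period: the transfusion arms are compared "in terms of the proportion of children with fatal outcome 28 days after randomisation".
- **Period of the costs.** The Health economics section measures costs "starting at randomisation and continuing for the duration of follow-up", applies unit costs "to obtain a cost per patient over the period of follow-up", and says that resource use "will be collected by carer interview at the 28-day, 90-day and 180-day visits". The length of follow-up is given under Study design and population: "Children will be enrolled over 2 years from 2 countries and followed for 6 months". No shorter cost period is given for R1.

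Mortality at 180 days is also available for R1, as a secondary outcome in Table 3: "Mortality: at 48 hours, 28 days, 90 days and 180 days (cumulative) where not the primary outcome".

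**The concern.** A cost-effectiveness comparison needs costs and effects counted over the same period. Taken together, these sections do not provide that for R1. A child who is re-admitted and dies at day 60 adds the re-admission to the cost side and is counted as a survivor on the effect side.

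The direction of the distortion depends on what happens after day 28. Suppose the strategy that gives more blood costs more. If it only postpones some deaths past day 28, the R1 cost per death averted looks too favourable. If it also prevents later deaths, the same quantity looks too unfavourable. Costs after day 28 are not negligible by the trial's own planning: the sample size section assumes a 12.5% cumulative rate of re-admission, relapse and re-transfusion by six months, in addition to deaths.

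**Working it through.** **1. The two periods side by side**

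| Comparison | Costs counted | Deaths counted |
|---|---|---|
| R1 (transfusion) | randomisation to day 180 | to day 28 |
| R2, R3 (supplement, cotrimoxazole) | randomisation to day 180 | to day 180 |

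For R1 the gap is 180 - 28 = 152 days.

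**2. What can be calculated.** The article states no cost and no cost-effectiveness figure, so there is nothing to reproduce and no ratio to compute. Only the change in the effect (the risk difference) can be illustrated.

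**3. Inputs from the Sample size section**

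- Transfusion versus none, uncomplicated stratum: 9% halved to 4.5%, a 28-day difference of 4.5 points.
- 30 versus 20 ml/kg: 13.67% reduced by 30% to 9.57%, a 28-day difference of 4.1 points.

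**4. Why late mortality must be assumed.** The Background cites 9-10% in-hospital and 12% six-month mortality, but from different sources, and in-hospital is not day 28. The planned four-week mortality already averages 0.5 × 9% + 0.5 × 16% = 12.5%, above that 12%. The six-month rates used for R2/R3 are 9% + 12.5% = 21.5% and 16% + 12.5% = 28.5%, where the 12.5% is the non-fatal events, so no late deaths are added. The article therefore yields no usable mortality between day 28 and day 180, overall or by arm.

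**5. Formula.** With r the 28-day risk and d the assumed risk of death from day 28 to day 180 among survivors:

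180-day risk = r + (1 - r) × d

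For a fixed cost difference, cost per death averted on the 28-day effect divided by that on the 180-day effect equals (180-day difference) / (28-day difference).

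Example, transfusion versus none, d = 6% in both arms: 0.09 + 0.91 × 0.06 = 0.1446; 0.045 + 0.955 × 0.06 = 0.1023; difference 0.0423; 0.0423 / 0.045 = 0.94.

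**6. Results (all late risks are assumptions)**

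| Late risk, comparator / more blood | Transfusion vs none: 180-day difference (factor) | 30 vs 20 ml/kg: 180-day difference (factor) |
|---|---|---|
| 2% / 2% | 4.41 points (0.98) | 4.02 points (0.98) |
| 6% / 6% | 4.23 points (0.94) | 3.85 points (0.94) |
| 6% / 4% | 6.14 points (1.36) | 5.66 points (1.38) |
| 4% / 6% | 2.41 points (0.54) | 2.13 points (0.52) |
| 6% / 8% | 2.32 points (0.52) | 2.05 points (0.50) |

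A factor of 1.38 means that the 28-day effect overstates cost per death averted by 38% relative to the 180-day effect. A factor of 0.50 means that it understates it by half.

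**The case against.** The strongest reply is that no single sentence sets 180-day costs over 28-day deaths. The Statistical analysis section links cost to outcome without naming a cost period, resource use is also collected at day 28, and a condensed article may leave the pairing to a fuller plan. This stands in part: a fuller plan could align the periods. But the article is not silent. It defines the cost per patient over the whole follow-up and the effect as the primary outcome, so an analyst who follows it obtains the mismatch.

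Second, the first secondary objective concerns cost-effectiveness in reducing early mortality, which supports a 28-day effect for R1. That stands, but a 28-day effect then needs 28-day costs.

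Third, a cost-utility analysis and decision-analytic modelling are also planned. Differences in trial endpoints, among them 180-day mortality, could enter the model, and quality-adjusted survival gives a common scale. This softens the effect on the overall economic conclusion. It adds to the within-trial analysis and does not replace it, and the extrapolation is described as starting beyond trial follow-up.

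A reader might also infer that the article will rank R1 ratios against R2 and R3 ratios, and that the ranking would be invalid. The article does not support this. No section states such a ranking, the objective is limited to early mortality, and the reference to alternative forms of management can mean the arms within one comparison.

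**Conclusion.** The concern holds as a mismatch of periods in the within-trial R1 analysis: costs to day 180, deaths to day 28, and nothing in the article that aligns them. It does not affect R2 or R3, nor any clinical primary result.

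Its size cannot be established from the article. If late mortality is equal between arms at an assumed 2% to 6%, the effect shrinks by about 2% to 6%, which is small. Shifts of roughly -50% to +38% require a 2-point difference in late mortality between arms, for which the article gives no figure. A reader might subtract the Background's in-hospital mortality from its six-month mortality to get a late risk of 2 to 3 points. That does not work, because the two rates come from different sources and the planned four-week mortality already exceeds the six-month figure. The larger shifts show what is possible and are not a forecast. This is a minor point that is worth settling before results are seen, since choosing the period afterwards could influence the conclusion.

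**What to change.** Add one sentence to the health economics plan: the within-trial R1 analysis relates costs to day 180 to mortality to day 180, and any 28-day R1 analysis, which suits the early-mortality objective, uses costs cut at day 28.

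No new data are needed. Mortality at 180 days is already a secondary outcome, children lost to follow-up are to be traced for vital status, and the 28-day resource-use interview allows the cut. The drawback is that the 180-day mortality difference may be slightly less precise than the 28-day one, since the sample size section assumes 6% loss to follow-up by six months.
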